### Tertiary outcomes

See Table 2 for priority ordering. We allow for nonlinear change as described above. If possible we adjust for values before treatment [40, 43]. The confirmatory and the exploratory model of periotest for teeth:

For tertiary outcomes other than periodontal or peri-implant conditions, we expect differences between groups before housing in group B (time points t_1_ and t_2_) but no differences after that (time points t_4_-t_6_). Thus, we present only confirmatory analyses. The model for food frequency questionnaire at time points t_1_ and t_2_:

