## Methods/design

### Study aim and design

The objectives of this study are to show that (1) immediately loaded (with housings)/restored (soft relining) mini-implants show more bone loss and less success than delayed loaded strategic mini-implants, (2) strategic mini-implants improve patients’ quality of life, patients’ satisfaction, chewing function, retention of the denture, and periodontal health of remaining abutment teeth. However, the improvements in the immediately loaded group will occur faster than in the delayed loaded group.

The protocol of this multi-center randomized parallel-group clinical trial follows the SPIRIT guidelines [31]. The study was designed according to the Good Clinical Practice guidelines (ICG-GCP) and the principles of the Declaration of Helsinki as revised in 2008.

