**Fig. 4 Fig4:**
[figure not shown]
Organization chart of the trial

Tertiary outcomes arePeriodontal and peri-implant conditions (probing depths, bleeding on probing (BOP), modified plaque index, modified sulcus bleeding index (mod. SBI), tooth and implant mobility measured by Periotest and Osstell)Oral health related quality of life (measure: short German version of the oral health impact profile (OHIP-G14) [33] and Patient’s satisfaction with the PRDP (Likert scale: totally satisfied - not at all satisfied) [34]Food frequency and avoidance questionnaire will be completed by the patients to evaluate the nutrition of the patients [35]Chewing efficiency will be quantified with colour-mixing ability test using a two coloured chewing gum (optoelectronical.evaluation of the ratio of unmixed colour pixels to the total pixel number in a fixed size template) [36]Dental and prosthetic complications: tooth loss, caries, endodontic treatment, implant- or tooth fracture, prosthesis fracture, loss of retention, housing detachments, loss of O-rings.

We hypothesized that after the placement of MDIs there will be significant improvements only in group A and not in group B at the baseline and at the 4- month follow-up examination. After the pick-up of the housings in group B there will be also significant improvements for patients of this group.

Examinations for all secondary outcomes are scheduled before implant placement (pre-treatment, exclusively outcomes No.1- 4), 14 days after implant placement (baseline) and 4, 12, 24 and 36 months after implant placement (Fig. 4). In addition, patients whose housings are picked-up after 4 months will be examined 14 days after the pick-up. A trained examiner of the leading treatment center not involved in the treatment of participants will perform all examinations. Additionally, a second examiner will survey the bone levels at implants on the radiographs.

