### Statistical methods

Because of the statistical power, we choose the continuous variable bone level to be the primary outcome measure. We differentiate confirmatory and exploratory analyses. Confirmatory analysis is related to differences between groups whereas exploratory analysis is related to the rate of change between groups (interaction between time and group), which yields low power test herein. However, we present the joint test of the factor group and the interaction between time and group. The explanations of the variables are outlined in Table 2.

**Table 2 Tab2:** Variables, measures, hypotheses, and methods of analysis

Variable	Measure, parameterization	Variable name for syntax	Level	Hypothesis	Points in time	Methods of analysis: Stata command (version 14)
1. Primary outcome						
a) Bone level	Radiographic bone levels around implants (mesial, distal, mm, continuous)	Bone level	Implant	Group A will show more bone loss than group B	(t_0_), t_4_, t_6_	Mixed model for continuous responses: mixed
2. Secondary outcome: Implant success	Modified criteria of Albrektsson (binary): composite variable on implant level	Success	Implant	Group A will show less success than group B	t_4_, t_6_	Mixed model for binary responses: melogit
a) Related to infection	Modified sulcus bleeding index (0–3 on 2 sites per implant)	SBI	Implant		t_1_, t_2_, t_3_, t_4_, t_5_, t_6_	Mixed model for ordinal responses: meologit
	Bleeding on probing (binary on 4 sites per implant)	BOP	Implant		t_1_, t_2_, t_3_, t_4_, t_5_, t_6_	Mixed model for binary responses: melogit
b) Clinical immobility	Clinical immobility of the implant (binary)	Mobility	Implant		t_1_, t_2_, t_3_, t_4_, t_5_, t_6_	Mixed model for binary responses: melogit
c) Pain	Persistent pain or discomfort (binary)	Pain	Implant		t_1_, t_2_, t_3_, t_4_, t_5_, t_6_	Mixed model for binary responses: melogit
d) Radiolucency	Evidence of peri-implant radiolucency (binary)	XLucency	Implant		t_4_, t_6_	Mixed model for binary responses: melogit
e) Survival	Implant in situ (binary)	ImplantLoss	Implant		Continuous time	Kaplan-Meier
3. Tertiary outcome						
a) Periodontal and periimplant conditions	Probing depths (mm, continuous on 4 sites per implant)	ProbingDepth	Implant	Group A will show higher values than group B	t_1_, t_2_, t_3_, t_4_, t_5_, t_6_	Mixed model for continuous responses: mixed

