	Probing depths (mm, continuous on 4 sites per tooth)	ProbingDepth	Tooth	Overall improvement at teeth, improvement occurred faster in group A than in group B	t_1_, t_2_, t_3_, t_4_, t_5_, t_6_	Mixed model for continuous responses: mixed
	Osstell (0–100, continuous on implant level)	Osstell	Implant	Group A will show lower values than group B until the fourth month, thereafter equalization between A and B	t_1_, t_2_, t_3_, t_4_, t_5_, t_6_	Mixed model for continuous responses: mixed
	Periotest (−8.0 - +50.0, continuous on tooth level)	Periotest	Tooth	Overall improvement at teeth, improvement occurred faster in group A than in group B	t_1_, t_2_, t_3_, t_4_, t_5_, t_6_	Mixed model for continuous responses: mixed
	Periotest (−8.0 - +50.0, continuous on implant level)	Periotest	Implant	Group A will show higher values than group B until the fourth month, thereafter equalization between A and B	t_1_, t_2_, t_3_, t_4_, t_5_, t_6_	Mixed model for continuous responses: mixed
b) Oral health related quality of life	OHIP-G14 questionnnaire (0–56, continuous)	OHIP	Patient	Overall improvement, improvement occurred faster in group A than in group B	t_1_, t_2_, t_3_, t_4_, t_5_, t_6_	Mixed model for ordinal responses: meologit
c) Patient’s satisfaction with the PRDP	Questionnnaire 8 items (Five-point Likert-scale, 8–40 continuous)	Satisfaction	Patient	Overall improvement, improvement occurred faster in group A than in group B	t_1_, t_2_, t_3_, t_4_, t_5_, t_6_	Mixed model for ordinal responses: meologit
d) Nutrition of the patients	Food frequency questionnaire (1–7)	FFQ	Patient	Overall improvement, improvement occurred faster in group A than in group B	t_1_, t_2_, t_3_, t_4_, t_5_, t_6_	Mixed model for ordinal responses: meologit
	Food avoidance questionnaire (binary)	FAQ	Patient	Overall improvement, improvement occurred faster in group A than in group B	t_1_, t_2_, t_3_, t_4_, t_5_, t_6_	Mixed model for binary responses: melogit
e) Chewing efficiency	Colour-mixing ability test with two coloured chewing gum (continuous)	Chewing	Patient	Overall improvement, improvement occurred faster in group A than in group B	t_1_, t_2_, t_3_, t_4_, t_5_, t_6_	Mixed model for ordinal responses: meologit
4. Exposure						
Group	2 categories		Jaw		t_0_	
5. Time variables						
TimePoint	0-6 for outcomes				0-6 for t_0_ –t_6_	
Week	Time [weeks]		Patient		Week	
SqrtWeek	Square root of week		Patient		Root of week	
Time			Patient		Continuous	
6. Confounder						

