### Publication

Analyses, presentations and publications will include the data of all study sites and not from one center alone. Results of prespecified outcome parameters will be published and released to the general medical community and patients regardless of the magnitude or effect direction of interventions.

The lead author, the principal investigator, the examiner, the statistician and at least one author per center will be listed as authors in presentations and publications. Additional professionals can be listed in the acknowledgement section. Professional medical writers will be not deployed.

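### For quality of life, satisfaction, nutrition and chewing, no A–B comparison at 12–36 months is clearly prespecified and the time-by-group term is given up, which conflicts with Table 2 and with the objective of faster improvement

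*Protocol article*

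**What the plan says.** All places are in the protocol article.

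- **Tertiary outcomes.** For outcomes other than periodontal or peri-implant conditions the text states "we expect differences between groups before housing in group B (time points t_1_ and t_2", then continues "but no differences after that (time points t_4_-t_6_). Thus, we present only confirmatory analyses". One model is then introduced: "The model for food frequency questionnaire at time points t_1_ and t_2".
- **Statistical methods.** The two terms are defined: "Confirmatory analysis is related to differences between groups whereas exploratory analysis is related to the rate of change between groups (interaction between time and group". The same paragraph promises, with no exception for any outcome, a joint test of group and of its interaction with time.
- **Table 2.** For OHIP-G14, satisfaction, food frequency, food avoidance and chewing efficiency the points in time are t1 to t6. The hypothesis is "Overall improvement, improvement occurred faster in group A than in group B". Four of the five are assigned an ordinal mixed model, and food avoidance a binary one.
- **Study aim and design.** The second objective, on patient outcomes, adds that "the improvements in the immediately loaded group will occur faster than in the delayed loaded group".
- **Outcomes.** Follow-up examinations run at "4, 12, 24 and 36 months after implant placement", after a first one at 14 days.
- **Publication.** "Results of prespecified outcome parameters will be published and released", whatever the size or direction of the effect.

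**The concern.** The analysis is narrowed because no later difference is expected. That expectation is part of what the trial should show: improvement that is faster, but not larger, means an early gap that later closes. An early comparison alone establishes the gap and says nothing about the closing.

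The early window is also the one in which the arms differ by construction. In group B the recesses in the prosthesis stay empty for four months (earlier soft relining is foreseen only for mucosal hyperplasia), while group A is loaded or soft-relined at once. Testing there is legitimate, because it is the stated hypothesis. But the first objective predicts more bone loss and less implant success in group A, with both assessed at 12 and 36 months. On the trial's own reasoning a late patient-level disadvantage in group A is possible, and for these five outcomes no A–B contrast is clearly laid down for that period. A late contrast chosen after the data are seen would carry less weight than one fixed now.

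**Working it through.** **1. The sections side by side.**

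| Element | Tertiary outcomes | Elsewhere |
|---|---|---|
| Visits in the model | t1, t2 (0.5 and 4 months) | Table 2: t1 to t6, up to 36 months |
| Time-by-group term | not presented, since only confirmatory analyses are kept | Statistical methods: joint test of group and interaction |
| Question | group difference before pick-up in B | Study aim and Table 2: improvement faster in A |

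By the article's definition, confirmatory means the group difference and exploratory means the interaction. The restriction therefore removes the interaction. The limit to t1 and t2 comes separately, from the expected null at t4 to t6 and from the visits named for the model. The visit at t3 (4.5 months) is scheduled only for patients whose housings are picked up at 4 months, so it is not a balanced A–B comparison and is left aside here.

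**2. What the early test can and cannot separate.** The simulation had 4,000 runs per scenario, 30 patients per arm, five visits (t1, t2, t4, t5, t6) and within-patient correlation of 0.3, 0.5 or 0.7. Early and late means were compared by two-sided 5 % t-tests. Effects of 0.8 SD are an assumption. Entries are the share of significant runs across the three correlations.

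| True A–B benefit (early / late, SD) | t1–t2 | t4–t6 | late minus early | one effect pooled over all five visits |
|---|---|---|---|---|
| Faster only (0.8 / 0) | 92–96 % | about 5 % | 98–100 % | 29–44 % |
| Better throughout (0.8 / 0.8) | 91–97 % | 93–99 % | 4–6 % | 94 % to over 99 % |
| Faster, then worse (0.8 / −0.8) | 91–97 % | 93–99 % | 100 % | 10–16 % |

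The early column is the same in all three rows. The late contrast singles out the first row, and its sign separates the other two. The interaction separates the second row from the rest. A single group effect over all visits without interaction would mostly miss the reversal, because early gain and late loss partly cancel.

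**3. Precision of a late comparison.** The article's only sample-size figure is for bone level: difference 0.4, SD 0.5, two-sided 5 %, 80 % power. An exact t-test calculation gives 25.5, rounded up to 26 per group, with power 80.7 % at 26, so the figure reproduces. With 40 allocated per group and 75 % response, 40 × 0.75 = 30 per arm.

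Treating an outcome as continuous, the 95 % CI half-width for A–B at one visit, in SD units, is t(0.975, 2n − 2) × √(2/n):

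- n = 30: 2.00 × √(2/30) = 2.00 × 0.258 = 0.52
- n = 26: 0.56
- n = 40: 0.45

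Averaged over t4 to t6 with an assumed correlation of 0.6, the factor is √((1 + 2 × 0.6)/3) = 0.856, so 0.52 × 0.856 = 0.44.

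With 30 per arm, a single-visit t-test has 48 % power for 0.5 SD and 86 % for 0.8 SD; 80 % power is reached at 0.74 SD.

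**The case against.** A reader might infer that the late randomised comparison has been abandoned, or that a late disadvantage of immediate loading would go unreported. The documents do not support that.

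- Nothing says that the 12- to 36-month data are left out of analysis or reporting.
- Under the article's definitions, the sentence on confirmatory analyses gives up the interaction, not the group contrast.
- Table 2 lists t1 to t6 with a named model for each of the five outcomes, the joint test is promised in general terms, and Publication commits to releasing results in either direction.
- The model with t1 and t2 is introduced for one outcome, food frequency, and the syntax of every model is missing from the text as read. A further late model cannot be excluded.

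It can also be said that testing early matches the hypothesis. Late harm is examined where the first objective places it: bone level and implant success at t4 and t6, survival in continuous time, peri-implant measures over t1 to t6. These five outcomes rank third, the added estimates would be imprecise, and an article condenses a fuller plan.

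Most of this stands, and it limits the point to patient-reported outcomes, nutrition and chewing. It does not remove the conflict. The visible prose names t1 and t2, gives an expected null as the reason, and introduces no late model. The publication commitment specifies no analysis. Sections that disagree on visits and on the interaction are a contradiction in the printed plan, not detail left to another document.

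The SD-based precision is only a guide, since the planned models are ordinal or binary. For food avoidance it does not describe the planned estimate.

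**Conclusion.** The point holds as a conflict between sections with a practical consequence. For five patient-level outcomes at three visits, spanning months 12 to 36 of a 36-month trial, no A–B comparison is clearly prespecified, and the term that would test faster improvement is given up. Followed as written, the t1–t2 analysis cannot tell faster from better and cannot detect a late reversal.

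The logical part rests on the text alone. The simulated percentages rest on assumed 0.8 SD effects, 30 per arm and continuous outcomes. The primary and secondary outcomes and the sample size are untouched. The change is worth making because it is cheap and decides what can be claimed about a stated objective.

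**What to change.** Reconcile Statistical methods, Table 2 and Tertiary outcomes as follows, before the late data are compared by arm.

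1. Keep t1–t2 as the confirmatory window for the five outcomes, and mark it so in Table 2, with t4–t6 as the reported exploratory window.
2. Replace the sentence that limits presentation to confirmatory analyses. Suggested wording: *For these outcomes the same ordinal or binary mixed model is also fitted at t4–t6. The A–B effect is reported with its 95 % confidence interval on the model's own scale, whatever its direction, together with the time-by-group (early versus late) term. Both are exploratory and carry no alpha.*
3. Say whether the joint test promised under Statistical methods applies to these outcomes.
4. State that a wide late interval is not evidence that the arms end at the same level.

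The cost is a few extra model fits on visits already scheduled and some wording. No new data, patients or clinical changes are needed. The downside is the modest precision shown above, which is why an estimate with its interval is asked for and not a test.

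### The improvement part of objective 2 has no described analysis for quality of life, satisfaction, nutrition and chewing efficiency: the planned models estimate A minus B, not change from before treatment

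*Protocol article*

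**What the plan says.** Study aim and design states objective 2 in two parts. The first is a before-after claim about all treated patients: "strategic mini-implants improve patients’ quality of life, patients’ satisfaction, chewing function, retention of the denture", together with periodontal health of the abutment teeth. The second is a between-arm claim: "the improvements in the immediately loaded group will occur faster than in the delayed loaded group".

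Table 2 carries both parts into the hypothesis for OHIP-G14, satisfaction, the two food questionnaires and chewing efficiency: "Overall improvement, improvement occurred faster in group A than in group B". For each it lists t1 to t6 and an ordinal or binary mixed model.

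The Outcomes section words the expectation arm by arm. At 14 days and 4 months, "there will be significant improvements only in group A and not in group B". It continues: "After the pick-up of the housings in group B there will be also significant improvements for patients of this group".

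Statistical methods defines two kinds of analysis: confirmatory (difference between groups) and exploratory (interaction of time and group). For tertiary outcomes other than periodontal or peri-implant conditions, the Tertiary outcomes section expects a group difference at t1 and t2 and none at t4 to t6, and concludes: "Thus, we present only confirmatory analyses". It then introduces one model, for the food frequency questionnaire, at t1 and t2. Pre-treatment values are measured, but they appear in the confounder block of Table 2 (at t-1) and as an adjustment where possible.

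**The concern.** A stated aim should have an analysis that estimates it. The first part of objective 2 is about change from before treatment. The analysis kept for these outcomes is a comparison of the two arms after treatment. Such a comparison can be null because both arms improved equally or because neither improved.

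The reason given for the restriction does not cover the gap. Expecting no group difference after the housings are picked up in group B is a reason to leave out the time-by-group interaction. It is not a reason to leave out overall change, which is the main question remaining at 12 to 36 months once the arms are expected to agree. Followed as written, the trial collects three years of data on these outcomes and describes no estimate of the improvement it set out to show.

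**Working it through.** The article gives no figure for objective 2; its sample-size calculation concerns bone level only. The check is therefore mainly a comparison of sections.

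**1. Claim against analysis**

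| Part of objective 2 | Quantity needed | Described analysis (five patient-level outcomes) |
|---|---|---|
| Implants improve the outcome | Mean at follow-up minus mean at t-1, both arms | None described |
| Faster in A than in B | A minus B at t1 and t2 | Confirmatory model adjusted for t-1 |

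**2. What the adjusted group contrast estimates**

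Write the model, on its linear-predictor scale, as: response at t = a + b × group + g × (value at t-1) + time terms.

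The coefficient b is A minus B at equal pre-treatment values. If both arms change by the same amount c, then b = 0 for every c, including c = 0. So b carries no information about c.

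**3. Would using all of t1 to t6 close the gap?**

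Let m(k) be the mean at time k. Then

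m(k) − m(−1) = [m(1) − m(−1)] + [m(k) − m(1)].

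A time effect over t1 to t6 recovers only the second bracket. t1 is 14 days after placement, when group A already has housings or a soft reline, so any change in group A before t1 falls in the first bracket. Only a model with t-1 among the responses includes it.

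**4. Contrast with the primary outcome**

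For bone level, the Primary outcome section adds t0 to the dependent variable in an exploratory model, so that change to 12 and 36 months can be read. No such model is described for the five outcomes here.

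**5. Table against text**

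Table 2 lists t1 to t6 for all five. The text names t1 and t2, explicitly for food frequency only. Extending that limit to the other four is an inference from the sentences before it, and the model syntax is not in the available text. Either way, table and text need to agree.

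**6. Is the missing estimate feasible?**

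Inputs: 80 patients and a 75% response rate (Sample size section), so 80 × 0.75 = 60 responders. Test: paired t-test, two-sided 0.05, 59 degrees of freedom, noncentrality d × √60 with √60 = 7.746. The standardized change d is assumed; the article gives none.

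| d (assumed) | Noncentrality | Power |
|---|---|---|
| 0.3 | 2.32 | 63% |
| 0.4 | 3.10 | 86% |
| 0.5 | 3.87 | 97% |

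The pooled before-after change could be estimated usefully unless it is small.

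**The case against.** The strongest reply is that these outcomes are not left without analysis. Table 2 gives each a hypothesis, a mixed model and six time points. The between-arm part of objective 2 is served by the t1 and t2 contrast, and the Tertiary outcomes section announces both a confirmatory and an exploratory model for Periotest at teeth. All of this stands. A reader might infer that objective 2 has no analysis at all; the article does not support that, and the gap is confined to the improvement part for the five outcomes named.

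A second reply is that change from before treatment is the kind of summary an article leaves to the analysis plan. That would hold if the article were silent. Instead it states a restriction to between-group analyses, after defining a scheme in which neither type of analysis is a before-after contrast.

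A reader might also infer from "there will be significant improvements only in group A and not in group B at the baseline and at the 4- month follow-up examination" that the trial will declare the arms different when one within-arm test is significant and the other is not. The article does not support this either. The sentence is a hypothesis, and the planned test is a direct group contrast, so no false-positive rate should be attached to it. Its wording still does not match that test.

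Nor should the unused visits be overcounted: t3 is scheduled only for patients whose housings are picked up at four months. Chewing efficiency is a measured colour-mixing test, so the point is not confined to patient-reported outcomes.

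Finally, the Discussion explains that there is no arm without implants and concedes that excluding satisfied patients may bias answers upward. Any before-after estimate is therefore weak evidence that implants cause improvement. That limits what can be claimed, but it does not remove the need to estimate a quantity the article names as an objective.

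**Conclusion.** The point holds in limited form. For OHIP-G14, satisfaction, food frequency, food avoidance and chewing efficiency, the improvement part of objective 2 has no described analysis, and Table 2 and the Tertiary outcomes section are not aligned on time points. The faster-in-A part does have an analysis.

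This rests on reading confirmatory as Statistical methods defines it, and on the pre-treatment value being a covariate only, as Table 2 places it. A separate analysis plan that already puts t-1 among the responses would close the gap, but the article would then need correcting to agree with it.

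The consequence is moderate. These are tertiary outcomes, and the primary and secondary analyses are unaffected. The change should be made because one stated aim depends on it.

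**What to change.** - Keep the between-group contrast at t1 and t2, adjusted for the pre-treatment value, as the test of faster improvement in A.
- Add one model per outcome with t-1 among the responses, as bone level already does with t0. Report change from t-1 to t4, t5 and t6, overall and by arm, with 95% confidence intervals.
- Label these results as uncontrolled before-after estimates, because there is no implant-free arm and satisfied patients were excluded.
- Align the time points in Table 2 with those in the Tertiary outcomes section for all five outcomes.
- Reword the hypothesis in the Outcomes section as a difference between arms at t1 and t2.

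The cost is some wording and one further model per outcome, on data already scheduled for collection. The downside is a little more analysis for evidence that remains weak on causation.
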